## Abstract

**Background:**

Active participation in intellectual leisure activities such as calligraphy helps prevent cognitive decline and dementia, but the underlying mechanisms are not fully understood. With disrupted functional connectivity (FC) of default mode network (DMN) associated with cognitive decline, we speculate that intellectual activities might optimize cognitive function through modulating FC of DMN. This two-arm single-blind randomized controlled trial aims to identify the effects of increasing practice of calligraphy on cognitive function and FC of DMN in people with subjective cognitive decline (SCD).

**Methods:**

One hundred twelve community-living Chinese aged 55 to 75 years old with SCD but without mild cognitive impairment or dementia and with prior practice of calligraphy as defined by 1 h of calligraphy per week will be recruited through elderly social centres in Hong Kong and randomized into either control or intervention group. The control group will continue with their usual practice of calligraphy, whereas the intervention group will double their practice of calligraphy. Measurement of cognitive outcomes and neuroimaging on resting-state FC will be performed at baseline and in 6 months. Repeated measures analysis of variance will be used to assess cognitive and FC changes, with time being the within-group factor, control/intervention as the between-group measure, and important covariates (age, sex, educational and occupational attainment, health, and other lifestyle factors) controlled for.

**Discussion:**

This study will shed light on the underlying neurocognitive mechanisms of how intellectual activities promotes cognitive maintenance. Our anticipated findings will provide evidence that reversing or slowing FC disruption by actively participating in intellectual activities is still possible for the at-risk individuals.

**Trial registration:**

Chinese Clinical Trial Registry ChiCTR1900024433. Registered on 11 July 2019.

## Administrative information

Note: the numbers in curly brackets in this protocol refer to SPIRIT checklist item numbers. The order of the items has been modified to group similar items (see http://www.equator-network.org/reporting-guidelines/spirit-2013-statement-defining-standard-protocol-items-for-clinical-trials/).

## Introduction

### Background and rationale {6a}

Dementia is a major health concern worldwide [1]. Given the rapidly ageing populations and the current absence of cost-effective disease-modifying treatment, finding ways to help at-risk individuals achieve cognitive maintenance and healthy ageing is of great clinical and public health importance [2–4].

Lifestyle modification such as participation in intellectual activities is increasingly recognized to be beneficial to cognition [5–14]. Our previous 6-year follow-up study of a large cohort of community-living dementia-free older adults found that while many reported engaging in leisure activities in their daily lives, those participating more in intellectual activities such as calligraphy, painting, reading books, and playing board games, cards and Mahjong were at a lower risk of incident dementia, independent of educational attainment, other health behaviours such as social and physical activities, physical and psychiatric comorbidities, and sensory impairments [15]. Higher level of participation in intellectual activities might serve as a useful, economical, and relatively safe non-pharmacological intervention for achieving cognitive maintenance in the at-risk older adults. Nevertheless, the underlying mechanisms of how intellectual activities slow cognitive decline are not fully understood [16].

Default mode network (DMN) is an interconnected set of different brain regions including precuneus/posterior cingulate cortex (PCC), medial prefrontal cortex (mPFC), lateral temporal cortex (LTC), inferior parietal lobe (IPL), and hippocampal formation which includes a proportion of parahippocampal cortex (HF+). It is most active when a person is at resting state (such as daydreaming and mind-wandering) but is deactivated when a person is engaged in external goal-orientated tasks [17]. Apart from serving as a sentinel which maintains a broad low-level focus of attention that monitors the external world for unexpected events, it is hypothesized to play a major role in thinking of self (e.g. self-reflection and autobiographical memory), mentalization (theory of mind, moral reasoning, and judgment), and remembering the past and envisioning the future [18].

With the help of resting-state functional magnetic resonance imaging (rs-fMRI), it is now recognized that DMN is organized into hubs and subsystems, with the activity of each brain region being highly correlated with the other when involving in the above functions. In particular, PCC serves as a hub that is activated in nearly all of the tasks described above; mPFC is involved in self-processing, mentalization, envisioning future goals, and decision-making (i.e. executive function, social cognition and flexibility in terms of higher cognitive function); LTC and HF+ are involved in memory; and IPL is involved in attention [18].

More importantly, different studies have shown that disruption of DMN, such as decreased functional connectivity (FC) in PCC and HF+, is present in people with clinical Alzheimer’s disease (AD) [19, 20]. It matches with not only the clinical presentation (i.e. poor memory and attention) but also other pathophysiological features of AD (e.g. hippocampal and medial temporal lobe atrophy as shown in structural MRI, and hypometabolism and beta-amyloid plaque accumulation in regions that overlap with disrupted DMN as shown in positron emission tomography) [20, 21]. Recently, increasing evidence shows that disruption of DMN is detected even in subjective cognitive decline (SCD), with decreased FC beginning in the posterior DMN, and becomes more pronounced and gradually progresses to other regions in mild cognitive impairment (MCI) [22–24]. These suggest that FC disruption appears very early in the course of AD and might be used in conjunction with other biomarkers to identify the severity and predict the progression of AD.

Given the importance of FC changes in the development of dementia, we propose to conduct a randomized controlled trial (RCT), with the aim to test whether increasing participation in habitual intellectual activities promotes cognitive maintenance via strengthening FC of DMN. In this study, calligraphy is chosen as the activity of interest, given its high prevalence of practice among cognitively active older adults in our locality and its popularity among those attending the elderly social centres. It has simultaneous involvement with different cognitive domains including attention and concentration, memory, spatial orientation, executive function, and eye-hand coordination, with evidence of improving global cognitive function [25, 26]. We will compare changes in cognitive function and FC following doubling of the usual practice of calligraphy for 6 months in community-living Chinese adults with SCD and prior practice of calligraphy.

Our study will shed light on the underlying neurocognitive mechanisms of how intellectual activities modulates cognitive function. More importantly, our anticipated findings may provide evidence that reversing, slowing, and/or compensating for FC disruption is still possible in SCD despite network dysfunction may have already been present in this early stage of AD. These will help support and extend previous literature that having greater participation in intellectual activities could potentially optimize cognitive reserve and strengthen resilience towards cognitive decline.

### Objectives {7}

The objectives of this study are:
To examine the effect of doubling the usual practice of calligraphy on global cognitive function in people with SCD;To examine the effect of doubling the usual practice of calligraphy on FC within DMN in people with SCD; andTo examine the correlation between cognitive and FC changes.

### Trial design {8}

This study is a two-arm, parallel-design, single-blind RCT of 6-month calligraphy practice conducted in Hong Kong. Participants will be randomized in a 1:1 ratio to either the intervention or control group. The framework of our trial is to test the superiority of doubling the “dosage” of calligraphy practice (*vs* maintaining on the same “dosage”) on cognitive function and FC of DMN.

## Methods: Participants, interventions and outcomes

### Study setting {9}

Community-living Chinese individuals aged 55 to 75 years old with SCD and prior practice of calligraphy will be recruited through advertisement in elderly social centres in Hong Kong. Participants will practise calligraphy in their usual setting, either at their own home or in elderly social centres.

### Eligibility criteria {10}

#### Inclusion criteria

Before recruitment, potential participants will be screened for presence of SCD as defined by (i) Hong Kong Chinese version of Montreal Cognitive Assessment (HK-MoCA) score of > 25, which is above the cutoff scores for MCI in younger-old adults with high education level [27], and (ii) Abbreviated Memory Inventory for Chinese (AMIC) with at least 1 positive answer to the 5 screening questions [28].

In addition, the potential participants will be screened for any practice of calligraphy, as defined by having at least 1 h of calligraphy per week, in the previous 6 months. There is no restriction on the form of calligraphy, but they are expected to have their calligraphy practice in a quiet environment, and their calligraphic writing should involve brush handwriting by tracing the strokes and structures of the characters displayed in a mixture of traditional calligraphic styles [29].

#### Exclusion criteria

Exclusion criteria include non-Chinese ethnicity; living in care homes; having history of stroke, traumatic brain injury, Parkinson’s disease, MCI, or clinical dementia; taking drugs that affect cognition (e.g. benzodiazepines, anti-dementia medication, etc.); having history of depression, bipolar affective disorder, psychosis, or substance abuse; already attending other cognitive intervention programs or having regular participation in painting (at least 1 h of painting per week); significant impairments in communication or writing; and having no prior practice of calligraphy.

### Who will take informed consent? {26a}

Trained research assistant will obtain written informed consent from all participants before participation. Our research assistant will first explain to eligible participants our programme in detail (aims, requirements, length of study, etc.). Information sheet will be provided so that eligible participants have a clear idea of the expected commitment before deciding to participate. Written informed consent will be obtained prior to participation.

### Additional consent provisions for collection and use of participant data and biological specimens {26b}

All participants will be screened for any potential contraindications to plain MRI brain scan (metallic implant, pacemaker, and claustrophobia) and explained about the MRI brain scan as part of our baseline and follow-up assessment. Those who have contraindications or refuse to receive MRI brain scan will not be recruited. Information sheet will be provided so that eligible participants have a clear understanding of the need to undergo plain MRI brain scan. Written informed consent for MRI brain scan will be obtained prior to participation. This trial does not involve collecting biological specimens for storage.

## Interventions

### Explanation for the choice of comparators {6b}

The aim of this study is to test if increasing habitual participation in intellectual activities will optimize cognitive function and brain network in older adults. Therefore, we design the intervention as doubling the usual practice of calligraphy and the control as maintaining the usual practice.

### Intervention description {11a}

Participants will be randomized in a 1:1 ratio to one of the following arms.
Control group: Participants will continue their usual practice of calligraphy in the same manner (i.e. same frequency, duration, style, and environment).Intervention group: Participants will continue their usual practice of calligraphy in the same manner, with the exception of doubling the amount of time spent in calligraphy.

### Criteria for discontinuing or modifying allocated interventions {11b}

Adverse events are expected to be minimal in this study, as no drug treatment or invasive procedure is involved, and the intervention (calligraphy) is already familiarized to the participants. Nevertheless, mild discomforts such as fatigue or muscle soreness due to prolonged sitting and writing and headache or eye soreness due intense concentration in calligraphy practice may be experienced by some participants. These potential discomforts will be explained to participants before signing consent. Participants will be advised to report to our research assistant any health problems or suspected adverse events during the study period. All complaints with regard to our intervention will be documented, and any adverse events potentially due to our intervention will be assessed and followed by the principal investigator. The intervention will be stopped immediately if the reported event is considered to be related.

### Strategies to improve adherence to interventions {11c}

To ensure compliance of calligraphy practice during the 6-month intervention period, participants from both groups will be asked to WhatsApp or email the research assistant a snapshot of their work and the amount of time they spend in calligraphy each time they finish practicing. Upon receiving their work, the research assistant will acknowledge receipt of their work and log but will not give them any feedback on their work. Those who do not have smartphones or internet access will be asked to record in a diary the date and amount of time spent on their work each time they finish practising calligraphy, and to hand in their diary and work to the research assistant bi-monthly for review of compliance.

### Relevant concomitant care permitted or prohibited during the trial {11d}

Individuals already attending other cognitive intervention programs will be excluded from participating in this study. Participants will be advised to continue their usual lifestyle, with the control group also maintaining on their habitual practice of calligraphy but the intervention group doubling on their calligraphy practice. They will also be advised not to attend other intervention programs or take medications that might affect their cognition and confound the results (e.g. brain tonics) during the study period.

### Provisions for post-trial care {30}

Serious adverse events or permanent harm done to the participants are highly unlikely in this study, as no drug treatment or invasive procedure is involved, and the participants have already been practising the intervention (calligraphy) prior to our study. Mild discomforts as described earlier are likely to be self-limiting and disappear with rest. Nevertheless, all complaints with regard to our intervention will be documented, and any adverse events potentially due to our intervention will be assessed and followed by the principal investigator. The intervention will be stopped immediately if the reported event is considered to be related, with referral to seek medical attention provided by the principal investigator.

### Outcomes {12}

#### Primary cognitive outcome

Global cognition will be assessed by the Chinese version of the Alzheimer’s Disease Assessment Scale-Cognitive Subscale (ADAS-Cog) [30], an objective cognitive test widely used in assessing global cognition even at the milder stages of AD progression.

#### Secondary cognitive outcomes

To increase the sensitivity of detecting important cognitive changes in our participants, additional assessments will be performed to assess the global and specific cognitive domains. Global cognition will be assessed by the HK-MoCA, a locally validated cognitive screening test to detect early memory and executive deficits in MCI [27], and the Memory Inventory for Chinese (MIC), which is a locally validated 27-item questionnaire on detecting SCD [31]. Regarding the specific cognitive domains, attention will be assessed by the digit span forward (DSF) test and the part A of trail making test (TMT-A); learning and memory will be assessed by the 10-min delayed recall and digit span backward (DSB) tests; and executive functioning will be assessed by the part B of trial making test and the Chinese verbal fluency test (CVFT) [32–36].

#### Primary neuroimaging outcome

Assessment and analysis of FC of DMN will be conducted based on the protocols developed by our team as reported previously [37, 38].

##### Data acquisition

Structural MRI (sMRI): Participants will be scanned using a 3 T MRI scanner with an 8-channel SENSE head coil (Achieva, Philips Medical Systems). A series of 3D high-resolution T1-weighted structural images will be collected for each participant with the following parameters: repetition time (TR) 7.4 ms, echo time (TE) 3.4 ms, flip angle 8°, voxel size 1.04× 1.04× 0.6 mm^3^, total scan time 8 min.Resting-state functional MRI (rs-fMRI): During the rs-fMRI session, participants will be instructed to relax, stay awake, and hold still without falling asleep. In each scanning sequence, a series of 40 axial T2- weighted gradient echo-planar images (TR= 3000 ms, TE=25 ms, flip angle=90°, field of view (FOV)=230× 230 mm^2^, in-plane resolution=2.4× 2.4 mm^2^, matrix=96× 96, slice thickness=3 mm) will be captured. A total of 120 time points of rs-fMRI will be acquired for each participant.

##### Data preprocessing and analysis

Preprocessing of rs-fMRI images will be conducted by Statistical Parametric Mapping software (SPM12, http://www.fil.ion.ucl.ac.uk/spm/software/spm12/) and resting-state fMRI data analysis toolkit (REST, http://restfmri.net/forum/REST_V1.8) [39] embedded in MATLAB R2016a. The first 5 volumes of each functional time series will be discarded because of the instability of the initial MRI signal and initial adaption of participants to the situation. The remaining rs-MRI data will be subsequently corrected for slice timing and realigned to the first image by rigid-body head movement correction. Then, the rs-fMRI images are coregistered to high-resolution T1 images and normalized to standard stereotaxic anatomical Montreal Neurological Institute (MNI) space. The normalized volumes are spatially smoothed using an isotropic Gaussian filter of 8-mm full width at half maximum. The time course in each voxel will be detrended to correct for linear drift over time. Nuisance signal (whole brain, white matter, cerebrospinal fluid and six motion parameters) will be regressed out from the rs-fMRI time series. Temporal filtering with a band of 0.01–0.08 Hz will then be conducted to the time series of each voxel to reduce the impact of low-frequency drifts and high-frequency noise.

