#### Covariates

Sociodemographic factors (age, sex, educational level, occupational attainment, employment status, marital status, and social network), physical comorbidities (as assessed by Chronic Illness Rating Scale), health behaviours (smoking and drinking, type and amount of other leisure activities, including social, physical, recreational, and intellectual activities, as assessed by Lifestyle Questionnaire [45]), and adherence to intervention (assessed based on the records of their work) will also be measured and included in the analysis.

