#### Functional connectivity

The sample size is calculated based on a RCT of cognitive training on memory in people with MCI (*n*=72) in which individual FC maps for the hippocampal seed were generated based on correlations between the mean signal time course within each seed region and the rest of the brain [47]. Cognitive training was found to increase FC between the hippocampus and left superior frontal lobe compared to sham, and a positive correlation (*r*=0.33; *p*=0.005) between changes in hippocampal FC and changes in the memory domain was identified. Therefore, we estimate that a sample of 70 will achieve a power of 0.80 with alpha 0.05 (two-tailed). Assuming the same dropout rate, our initial calculation of 112 participants will yield enough power for the FC-cognition analysis.

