## Statistical methods

### Statistical methods for primary and secondary outcomes {20a}

Statistical analysis will be performed using IBM SPSS Statistics for Windows. Independent *t* test (for continuous variables) and chi-square test (for categorical variables) will be used to compare socio-demographics, clinical characteristics, lifestyle activities, cognitive functions, and resting-state FCs at baseline between the control and intervention groups for exploratory analyses. Repeated measures analysis of variance will be used to evaluate the cognitive and FC changes, with time being the within-group factor, control/intervention as the between-group measure, and covariates being controlled for. Association between cognitive parameters and FCs will be computed with correlational analyses. Intention-to-treat analysis and Bonferroni correction will be adopted.

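### As described in the article, the objective 3 correlation between FC change and cognitive change is not adjusted for change in head motion, so it is biased if motion change relates to both.

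*Protocol article*

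**What the plan says.** The section on data preprocessing and analysis sets out the imaging pipeline step by step, from discarded volumes to the filter band. Two of its steps concern motion. Images are "realigned to the first image by rigid-body head movement correction", and later "Nuisance signal (whole brain, white matter, cerebrospinal fluid and six motion parameters) will be regressed out from the rs-fMRI time series". Both act on one person's time series in one scan.

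The section on the primary neuroimaging outcome says that FC assessment and analysis "will be conducted based on the protocols developed by our team as reported previously [37, 38"]. Those sources are not shown.

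The Covariates section lists sociodemographic factors, comorbidity and health behaviours, and ends: "and adherence to intervention (assessed based on the records of their work) will also be measured and included in the analysis". It has no motion measure.

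The third objective is the correlation between cognitive and FC changes. For it, section {20a} says only: "Association between cognitive parameters and FCs will be computed with correlational analyses". It names no covariate for these correlations. The same section adds: "Intention-to-treat analysis and Bonferroni correction will be adopted". The number of tests is not given.

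The sample-size section on functional connectivity rests on an earlier trial in which "a positive correlation (*r*=0.33; *p*=0.005) between changes in hippocampal FC and changes in the memory domain was identified". From this it derives a sample of 70.

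**The concern.** Regressing six motion parameters out of a time series removes the part of the signal that is linear in those parameters within that scan. It does not ensure that the artefact left behind is equal from one person or visit to the next. A participant who is more restless or less well at T1 than at T0 may move more in the scanner and also test worse. FC change and cognitive change would then share a cause that has nothing to do with a neural link between them.

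Randomisation does not protect against this, because objective 3 relates two measured changes to each other and does not compare the arms. That correlation carries the trial's mechanistic claim and is the basis of its second sample-size calculation.

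What matters is *change* in motion. A stable difference between people in how much they move largely cancels when T0 is subtracted from T1.

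**Working it through.** **1. The plan's own figure.** Inputs from the sample-size section: r = 0.33, two-sided alpha 0.05, power 0.80. With Fisher's z, n = ((1.960 + 0.842) / atanh(0.33))² + 3, where atanh(0.33) = 0.3428. This gives 69.8, so 70, as stated. With 20% drop-out, 70 / 0.80 = 88, which 112 covers. No stated figure is in dispute.

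**2. Completers.** 112 × 0.80 = 89.6. I use 89.

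**3. Size of the spurious correlation.** Let a be the correlation of motion change with FC change, and b its correlation with cognitive change. If FC change and cognitive change are unrelated once motion change is held fixed, their expected unadjusted correlation is a × b. The documents give neither a nor b, so the values below are assumptions.

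**4. False-positive rate.** Under Fisher's z the test statistic has mean atanh(ab) × √(89 − 3) and unit variance. The two-sided 0.05 test rejects beyond ±1.960. For a = b = 0.3, atanh(0.09) × √86 = 0.0902 × 9.274 = 0.837, and the rejection probability is 0.133. The last column repeats the calculation at alpha 0.005, that is, Bonferroni for an assumed ten tests.

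| a | b | spurious r | rate at 0.05 | rate at 0.005 |
|---|---|---|---|---|
| 0.2 | 0.2 | 0.04 | 0.066 | 0.008 |
| 0.3 | 0.3 | 0.09 | 0.133 | 0.025 |
| 0.4 | 0.4 | 0.16 | 0.322 | 0.095 |

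If a or b is zero, ab = 0 and the rate stays at its nominal level.

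**5. Effect of adjustment.** In simulation (20,000 trials per scenario, n = 89), the partial correlation given motion change rejected in 4.8% to 5.2% of trials in every scenario run, up to a = 0.5 and b = 0.4. There the unadjusted test rejected in 47.6% of trials (46.8% by formula).

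**6. Cost in power.** At r = 0.33 and n = 89, the power of the unadjusted test is 88.9%. Losing one degree of freedom (√85 in place of √86) gives 88.5%.

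**The case against.** The strongest objection is that this argues from silence. The article refers to earlier team protocols and to a full protocol lodged with the registry. Either of these, or an analysis plan, could hold a motion limit or a motion covariate. Condensed articles often leave out such detail, and the covariate list describes participants and does not rule out image-quality terms. This stands as a limit on the claim: a reader might infer that the trial has no further motion control, and the documents do not support that. It does not dispose of the point. The article goes into such detail as the smoothing kernel and filter band, lists its covariates, and gives for objective 3 a correlation with no adjustment named.

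The magnitude is also wholly assumed. At 0.2 with each change, the excess over 0.05 is negligible. Associations of 0.4 may be too high in people with HK-MoCA above 25 and no history of stroke or Parkinson's disease, who are told to hold still and whose data have had whole-brain signal and six motion parameters regressed out. This stands. Nothing shown establishes that the associations are large, or that these steps reduce them to zero. The direction is open too: depending on the signs of a and b, the bias could mask a true link as well as create one.

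The rates at 0.05 are not those of the planned procedure, because Bonferroni will be applied. That also stands, and the last column of the table shows the effect. Correction lowers the absolute rates, but each remains above 0.005.

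Finally, a reader might infer that the randomised FC comparison is biased as well. The documents do not support this. Motion adds noise there and biases the comparison only if motion change differs by arm.

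**Conclusion.** The point holds as a conditional weakness of a stated method. As the article describes it, objective 3 will be tested by a correlation that is open to bias from change in head motion. The bias needs motion change to be related to both FC change and cognitive change. Under assumed associations of 0.2 to 0.4 with each, the spurious correlation is 0.04 to 0.16, against the planned 0.33. The corresponding false-positive rate is about 0.07 to 0.32 at an uncorrected 0.05 level with 89 completers. It is lower but still above nominal under Bonferroni, and not inflated if either association is zero.

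Objective 1 is not affected, and for objective 2 the expected effect is loss of precision. This is a minor, low-cost improvement and not an error in the sample size or in the pipeline.

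**What to change.** Compute mean framewise displacement at T0 and T1 from the realignment parameters that the pipeline already estimates. Report the objective 3 results as partial correlations adjusted for change in displacement.

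In the randomised FC comparison, keep displacement out of the main model. T1 motion is measured after randomisation, and adjusting for it could distort the arm effect if practice influences how still people lie. Use it there in sensitivity analyses only: one adjusting for displacement, and one repeating the comparison without scans above a single limit fixed before unblinding.

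The cost is one degree of freedom in the correlations, minor analysis work, and possibly a few scans left out of one sensitivity analysis. No new data are needed. If the earlier team protocols or an analysis plan already provide for this, a sentence saying so in the preprocessing section or in {20a} is enough.
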